### G2.2 Intention to treat analysis

The primary analysis of the clinical trial will be “intent to treat” (ITT) analysis based on the total cohort of randomized patients. This approach will be applied to the primary endpoint (live birth) as well as designated secondary endpoints. The difference between the incidence rates of live births for the two treatment groups will be examined by a two-sided test based on the standard Z-score (using the normal approximation to the binomial distribution). The common null hypothesis states that the effect of aspirin on the outcome is null compared to the placebo.

The secondary objectives (as described in Section A) with binary endpoints will be analyzed similarly as comparison of proportions. For binary outcomes such as pregnancy, the time to event may be of interest. In this case, survival analysis methods will be applied with the log-rank test for comparison of the two study treatment groups. For continuous outcome such as birthweight either parametric or non-parametric methods will be used as appropriate. If transformations to approximate a normal distribution are feasible, they will be carried out prior to the parametric analysis. The normality of the data will be examined both graphically using Q-Q plots and by formal tests (Wilks- Shapiro test). For data (either on original or transformed scale) assumed to be normally distributed the comparison of the two treatment groups will be carried out by a t-test. Alternatively if a non-parametric test is required, the Wilcoxon-Mann-Whitney test will be used.

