The following Tables 3 and 4 present results of power calculations for various interim looks plans for the EAGeR trial. These demonstrate the implications of different choices for the number and timing of interim looks. We assume throughout an alpha level of 0.05 and a sample size of 1600 women divided equally to the aspirin and placebo arms of the trial. Previously published studies suggest that for the control group a probability of about 0.70 - 0.80 for live birth given pregnancy ( $P_{preg}$ ) can be expected. Further, the probability of implantation per cycle ( $P_{implant}$ ) was assumed to be constant and in the range between 0.175 and 0.25. Figure 4 shows the probability of live birth (PLB) considering six cycles of menstruation (including both active and passive follow-up):

$$PLB = P_{preg} P_{implant} \sum_{c=1}^6 (1 - P_{implant})^{c-1}$$

**Figure 4.** Probability of live birth versus implantation probability per menstrual cycle

[figure not shown]

Hence a conservative estimate for the live birth rate would be a combination of implantation rate or 17.5% per cycle and a probability of live birth given pregnancy of 70% yielding an estimated value of  $PLB = 0.479$ . The final calculations will be done after the population from which participants are drawn will be identified. A refinement of the calculation can easily incorporate non-fixed probabilities of implantation per cycle

In the following, we consider a range of probabilities for the placebo + folic acid arm of 0.46, 0.48 and 0.50. The effect of the intervention will be measured as the rate ratio (RR) of live birth in the aspirin + folic acid arm compared to placebo + folic acid. We consider effect sizes of 1.15, 1.20 and 1.25. The calculations were preformed using PASS software. Table 3 presents the resulting power for no interim looks and Table 4 shows the power for one or two interim looks for selected outcome probabilities and effect size.

**Table 3.** Power for comparing live birth rates in treatment and placebo groups with no interim looks.

| Live Birth Probability in placebo arm | Live Birth Rate Ratio to be Detected |            |      |
|---------------------------------------|--------------------------------------|------------|------|
|                                       | 1.15                                 | 1.20       | 1.25 |
| 0.46                                  | .77                                  | .96        | .99  |

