| 0.48                                  | .81                                  | .97 | 1.0  |
| 0.50                                  | .84                                  | .98        | 1.0  |

Table 3 shows for example that with 800 women in each treatment arm, we have >80% power to detect effects  $\geq 1.15$  for an assumed overall live birth rate of 0.48 in the placebo group.

Table 4 gives the power for one or two interim looks and the Z-score boundaries, assuming PLB = 0.48 in the placebo arm and a rate ratio of 1.20. For the period 16 – 56 months when live births accumulate, an interim look at 0.45 and 0.6 of the way correspond to 18 and 24 months into the planned recruitment period. In other words, stopping at month 18 of recruitment (24th month of the trial) will “save” the last 6 months of recruitment while by 24 months of recruitment (30th month of the trial) the target sample size should be reached and the stopping will apply to cessation of follow-up and data collection. Alternatively if at this stage aspirin is shown to be effective one could switch the placebo patients to aspirin and continue the follow-up. The decision to stop early will not be made solely on the basis of these statistical tests but will be made by the DSMB taking into account all available information including evaluation of secondary outcomes and ethical issues.

**Table 4.** Power for one or two interim looks assuming PLB = 0.48, RR = 1.2

| Number of interim looks | Time of interim looks | Boundaries  | Power |
|-------------------------|-----------------------|-------------|-------|
| 1                       | 0.45                  | $\pm 2.571$ | 0.490 |
|                         | 1.00                  | $\pm 2.010$ | 0.964 |
| 1                       | 0.60                  | $\pm 2.366$ | 0.718 |
|                         | 1.00                  | $\pm 2.038$ | 0.963 |
| 2                       | 0.45                  | $\pm 2.571$ | 0.490 |
|                         | 0.60                  | $\pm 2.485$ | 0.696 |
|                         | 1.00                  | $\pm 2.050$ | 0.962 |

Thus for example, compared to the naive power of 0.97, one interim look at 0.45 of events accumulation period will results in a very small loss of total power to 0.964

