##### *Prediction of live birth*

Various prediction models can be built for this binary event considering baseline and follow-up information. Since women were randomized to receive one of two treatments, we will initially develop separate models for the groups based on the intention to treat assignment with the population at risk being the complete study population. We propose a few modeling approaches as an example.

A model to predict the probability of live birth may be developed based on the information collected at the baseline visit such as demographic information, medical history, and time since last spontaneous abortion. Three methods can be used to build such a model: (a) Logistic regression (b) Neural networks (c) Regression trees. While logistic regression is a standard technique, the other two methods will allow us to consider more complicated associations between risk factors and outcome (e.g. interactions and optimal cut-off points) as well as discrete outcomes with several possible categories (e.g. early pregnancy loss, pregnancy complications, birth). These aspects may be especially interesting for the EAGeR trial where a number of sequentially occurring endpoints are evaluated.

Validation methods will be used to compare these approaches whereby the data will be divided randomly into a training (e.g. 2/3 of the data) and validation sets (e.g. 1/3 of the data). The models will be fit using the training set and their predictive ability will be compared on the validation set. ROC (receiving operating characteristic) curves will be used to compare the different models and determine which is to be preferred. The optimal probability threshold for the logistic and neural network models will be chosen using the Youden Index.

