### **I.3. Subject Population**

#### **A. Women and Minorities**

Women 18-40 years of age will be recruited for participation this study. All women who have experienced a pregnancy loss in the last 12 months will be provided with information about the study. In addition, information about the study will be posted in physician offices in the form of "tear-off sheets" or study brochures. No efforts will be made to exclude any women based on minority, racial, or ethnic status. Given the focus of this particular study, women will be the only participants in this study.

Participants will be requested to complete a brief questionnaire at the time of informed consent that identifies ethnicity and racial designation(s). The participant will be asked for ethnicity first and then will be able to identify one more racial designations.

The trial is potentially open to all women who fit the inclusion/exclusion criteria. The DCC will work with the clinical sites to identify potential sources of data to characterize as best as possible the race/ethnicity composition of the population to be screened for participation in the trial. Typically, trial populations do not accurately represent the target population. However, effort will be made to direct the screening to allow a heterogeneous group to be included. The DCC will generate monthly summaries to each site with the age and ethnic composition of the population screened and the group recruited. In case a growing imbalance develops, the issue will be discussed with the clinical sites and with the project officer to come up with necessary changes in recruitment strategies to minimize exclusion of minorities for any reason. No sub-group analysis is planned but statistical modeling of the data will assess the impact of age and race/ethnicity on study endpoints.

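### The primary live-birth test uses neither the randomization strata nor any baseline value; it is valid, but gives up a modest, cheaply recovered amount of precision

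*Supplement*

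**What the plan says.** Section G2.2 of the latest protocol version makes the primary analysis an intention-to-treat "analysis based on the total cohort of randomized patients", tested by a "two-sided test based on the standard Z-score (using the normal approximation to the binomial distribution". No covariate or stratum enters. The Interim Analysis chapter (1.1.1) builds its statistic Z(t) on the same raw difference in observed proportions.

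Randomization (D.5b) is stratified by clinical center and eligibility group. Group I is defined by a single spontaneous abortion before week 20 and within the last 12 months, at most one live birth, and no loss at or beyond 20 weeks. Group II is every other eligible woman.

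Baseline data (D.4) include demographics, detailed menstrual and reproductive history, and height and weight. Their stated uses for live birth lie outside the primary comparison. G.4 suggests prediction models from "information collected at the baseline visit such as demographic information, medical history, and time since last spontaneous abortion", fitted at first separately by arm. I.3 says that "statistical modeling of the data will assess the impact of age and race/ethnicity on study endpoints". G.4 mentions covariate adjustment for time-to-event secondary endpoints, but no section gives a covariate-adjusted treatment comparison for live birth.

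For power, G.3 states: "We assume throughout an alpha level of 0.05 and a sample size of 1600 women divided equally". On the placebo rate: "we consider a range of probabilities for the placebo + folic acid arm of 0.46, 0.48 and 0.50". On the effect: "We consider effect sizes of 1.15, 1.20 and 1.25".

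**The concern.** The plan thinks these baseline values worth modelling for live birth, yet leaves them out of the comparison that the trial exists to make. Two consequences follow. Outcome variation that age and reproductive history could explain stays in the standard error of the aspirin effect. And chance imbalance between the arms in anything that the strata do not control, age above all, passes into the estimate unadjusted.

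The randomization constrains balance on center and eligibility group, but the test takes no credit for it. Ignoring stratification factors in the analysis tends to make the test slightly conservative.

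What is at stake is a little power where the margin is thin. Table 3 gives 0.77 to 0.84 at a rate ratio of 1.15, before interim looks. The Interim Analysis chapter (1.2) reports 68% power at a placebo rate of 0.40 and the same ratio.

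**Working it through.** **Inputs from the documents.** Two-sided alpha 0.05; N = 1600, 800 per arm (G.3); placebo rate p0 = 0.48 with RR 1.15 or 1.20 (G.3); p0 = 0.40 with RR 1.15 (Interim Analysis chapter, 1.2). The reference case for Table 4 is "assuming PLB = 0.48 in the placebo arm and a rate ratio of 1.20".

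**Step 1: reproduce the plan's figures.** A pooled two-proportion Z-test with 800 per arm at p0 = 0.48 gives power 0.822, 0.971 and 0.998 for RR 1.15, 1.20 and 1.25. Table 3 states 0.81, 0.97 and 1.0. All nine cells agree within two points. With a continuity correction the RR 1.15 column becomes 0.774, 0.809 and 0.842, which rounds to the stated 0.77, 0.81 and 0.84.

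The interim chapter's own formula, θ = δ√N/(2σ), gives:

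- p0 0.48, RR 1.15: δ = 0.072, σ = 0.49845, θ = 0.072 × 40/(2 × 0.49845) = 2.889; power = Φ(2.889 − 1.96) = 0.824.
- p0 0.48, RR 1.20: θ = 3.864; power = Φ(1.904) = 0.971.
- p0 0.40, RR 1.15: θ = 2.43; power = 0.680.

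**Step 2: an assumption for prognostic strength.** The documents give none. For a normal score with AUC A, the separation is d = √2·z(A), and with about half the women having a live birth the share of outcome variance explained is R² = d²/(d² + 4):

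- A = 0.58: d = 0.286, R² = 0.020
- A = 0.60: d = 0.358, R² = 0.031
- A = 0.65: d = 0.545, R² = 0.069

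**Step 3: effect of adjustment.** An adjusted marginal risk difference has its standard error multiplied by about √(1 − R²). Power becomes Φ(θ/√(1 − R²) − 1.96). The equivalent number of extra women is 1600 × (1/(1 − R²) − 1).

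| Scenario | Crude | A = 0.60 | A = 0.65 |
|---|---|---|---|
| p0 0.48, RR 1.15 | 0.824 | 0.835 | 0.850 |
| p0 0.48, RR 1.20 | 0.971 | 0.975 | 0.980 |
| p0 0.40, RR 1.15 | 0.680 | 0.694 | 0.711 |
| Equivalent extra women | – | 51 | 119 |

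At A = 0.58 the equivalent is about 33 women.

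A simulation of 4,000 trials per setting, with one normal score and a regression-adjusted risk difference with robust standard error, agrees. Power rose from 0.823 to 0.840 (A = 0.60) and from 0.820 to 0.853 (A = 0.65), with type I error 0.0505 and 0.052.

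**Step 4: how much the strata alone could give.** For two strata with shares w and 1 − w whose live-birth rates differ by D, R² = w(1 − w)D²/(p(1 − p)). Taking D = 0.10 and w = 0.5 (both assumed), R² = 0.25 × 0.01/(0.48 × 0.52) = 0.010. That is worth 1600 × (1/0.99 − 1) = 16 women. An eligibility-group term alone therefore recovers little unless the groups differ by much more. Most of any gain has to come from age and from finer reproductive history.

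**The case against.** The strongest reply is that nothing is broken. Under 1:1 stratified randomization the crude test is unbiased and holds its type I error. It is the test that Tables 3 and 4 assume, and it is easy to explain. At the case that G.3 uses for Table 4 and its conclusions, power is already 0.97 and adjustment adds less than one point. The p0 0.40, RR 1.15 case comes from a futility sensitivity exercise that the chapter itself presents as extreme. All of this stands.

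Three stronger readings are tempting, and the documents do not support them:

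- *That the baseline variables are strong predictors.* No section gives any association with live birth. G.4 says only that a model may be developed, as an example, and I.3 poses the effect of age and race/ethnicity as something to assess. The AUC range assumed here is itself weak discrimination.
- *That reproductive history is left entirely to chance.* D.5b builds number of losses, recency of loss and prior live births into the eligibility group. In group I the number of losses is one, recency is within 12 months, and live births are at most one. Stratification therefore already captures part of these variables. Age lies wholly outside the strata, and group II remains mixed.
- *That the whole gain of 50-120 women comes on top of the stratification.* It is measured against a Z-test that ignores the strata, so part of it is credit for balance that the randomization already provides.

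The cost is also more than a sentence. The interim chapter derives Z(t), σ, θ, conditional power and the futility bound from the crude difference.

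**Conclusion.** The point holds as a missed efficiency, not as an error. The primary test leaves out the strata and every baseline value, and no adjusted treatment comparison for live birth appears elsewhere in the plan.

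The size is modest and rests on an assumed AUC of 0.60-0.65: about 1 to 3 percentage points of power at RR 1.15, and under one point at RR 1.20. If baseline data discriminate less well, the gain shrinks in proportion. The calculation also assumes 1600 women with known outcome, as G.1 does, and no interim looks.

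The change is still worth making. RR 1.15 is one of the plan's own three effect sizes, G.3 claims high power for effects more modest than 1.2, and no new data are needed. Fixing the covariate list in advance also removes any scope for choosing covariates after the results are seen.

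**What to change.** In G2.2, prespecify as primary a standardized (marginal) risk difference and risk ratio for live birth from a logistic model. Include treatment, clinical center, eligibility group, age and a short fixed list of reproductive-history variables: prior live birth, number of prior losses, and time since last loss. State a robust or delta-method standard error, and simple imputation for missing baseline values (mean, or a missing category). Standardization keeps the rate-ratio and difference scales used in G.3 and the interim chapter.

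Keep the crude Z-test as a supporting analysis. Use the same adjusted statistic at the interim looks and the final analysis, and restate the interim chapter's formulas for Z(t), the drift and conditional power accordingly.

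The cost is a paragraph in G2.2, some extra programming and the restatement of those formulas. No further data collection or recruitment is involved.

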### **G.3 Interim analysis**

For a multi-year trial such as this one it is useful to examine the data as it accumulates in order to see if the study should be ended early or to catch any surprising developments. Such interim analysis needs to be planned formally. One of the most widely used procedures for interim analysis of a clinical trial is the  $\alpha$  spending function approach of Lan and DeMets. This method uses a function of time to specify the rate at which the total Type I error probability is to be spent during the trial interim looks so that this quantity does not exceed the desired overall Alpha level. For the EAGeR trial the spending function corresponding to the O'Brien-Fleming procedure will be used. The O'Brien- Fleming boundaries were chosen since for a given sample size they do not significantly change the overall power and are conservative early in the trial. By

conservative we mean that the proportions of success must be extremely different between the treatment arms to result in statistical significance early in the trial.

For our implementation the rate at which Type I error is spent is a function of elapsed time. We consider live birth as the primary trial endpoint and can expect events to start appearing approximately 10 months after subjects are randomized, that is month 16 of the trial. The accrual period will continue through month 40 while Phase II ends by month 57. Thus, for the interim analysis we consider the time interval of 16-56 month as the period when the primary outcome of live birth accumulates. Realistically though, only interim looks prior to month 40 of the trial will affect future recruitment while looks between 40 and 56 months can only affect decisions regarding continuing active or passive follow-up of subjects already enrolled in the trial.

The following Tables 3 and 4 present results of power calculations for various interim looks plans for the EAGeR trial. These demonstrate the implications of different choices for the number and timing of interim looks. We assume throughout an alpha level of 0.05 and a sample size of 1600 women divided equally to the aspirin and placebo arms of the trial. Previously published studies suggest that for the control group a probability of about 0.70 - 0.80 for live birth given pregnancy ( $P_{preg}$ ) can be expected. Further, the probability of implantation per cycle ( $P_{implant}$ ) was assumed to be constant and in the range between 0.175 and 0.25. Figure 4 shows the probability of live birth (PLB) considering six cycles of menstruation (including both active and passive follow-up):

$$PLB = P_{preg} P_{implant} \sum_{c=1}^6 (1 - P_{implant})^{c-1}$$

**Figure 4.** Probability of live birth versus implantation probability per menstrual cycle

[figure not shown]

Hence a conservative estimate for the live birth rate would be a combination of implantation rate or 17.5% per cycle and a probability of live birth given pregnancy of 70% yielding an estimated value of  $PLB = 0.479$ . The final calculations will be done after the population from which participants are drawn will be identified. A refinement of the calculation can easily incorporate non-fixed probabilities of implantation per cycle

In the following, we consider a range of probabilities for the placebo + folic acid arm of 0.46, 0.48 and 0.50. The effect of the intervention will be measured as the rate ratio (RR) of live birth in the aspirin + folic acid arm compared to placebo + folic acid. We consider effect sizes of 1.15, 1.20 and 1.25. The calculations were preformed using PASS software. Table 3 presents the resulting power for no interim looks and Table 4 shows the power for one or two interim looks for selected outcome probabilities and effect size.

**Table 3.** Power for comparing live birth rates in treatment and placebo groups with no interim looks.

| Live Birth Probability in placebo arm | Live Birth Rate Ratio to be Detected |            |      |
|---------------------------------------|--------------------------------------|------------|------|
|                                       | 1.15                                 | 1.20       | 1.25 |
| 0.46                                  | .77                                  | .96        | .99  |
| 0.48                                  | .81                                  | .97 | 1.0  |
| 0.50                                  | .84                                  | .98        | 1.0  |

Table 3 shows for example that with 800 women in each treatment arm, we have >80% power to detect effects  $\geq 1.15$  for an assumed overall live birth rate of 0.48 in the placebo group.

Table 4 gives the power for one or two interim looks and the Z-score boundaries, assuming PLB = 0.48 in the placebo arm and a rate ratio of 1.20. For the period 16 – 56 months when live births accumulate, an interim look at 0.45 and 0.6 of the way correspond to 18 and 24 months into the planned recruitment period. In other words, stopping at month 18 of recruitment (24th month of the trial) will “save” the last 6 months of recruitment while by 24 months of recruitment (30th month of the trial) the target sample size should be reached and the stopping will apply to cessation of follow-up and data collection. Alternatively if at this stage aspirin is shown to be effective one could switch the placebo patients to aspirin and continue the follow-up. The decision to stop early will not be made solely on the basis of these statistical tests but will be made by the DSMB taking into account all available information including evaluation of secondary outcomes and ethical issues.

**Table 4.** Power for one or two interim looks assuming PLB = 0.48, RR = 1.2

| Number of interim looks | Time of interim looks | Boundaries  | Power |
|-------------------------|-----------------------|-------------|-------|
| 1                       | 0.45                  | $\pm 2.571$ | 0.490 |
|                         | 1.00                  | $\pm 2.010$ | 0.964 |
| 1                       | 0.60                  | $\pm 2.366$ | 0.718 |
|                         | 1.00                  | $\pm 2.038$ | 0.963 |
| 2                       | 0.45                  | $\pm 2.571$ | 0.490 |
|                         | 0.60                  | $\pm 2.485$ | 0.696 |
|                         | 1.00                  | $\pm 2.050$ | 0.962 |

Thus for example, compared to the naive power of 0.97, one interim look at 0.45 of events accumulation period will results in a very small loss of total power to 0.964

Even with two interim looks there is very little power loss. Two interim looks at 18 and 24 months into the planned recruitment period yield a high total power of 0.962 and is the proposed plan for the trial.

The high power shown for assessing an effect size of RR =1.2 for the primary outcome of the EAGeR trial indicate that more modest effects could be detected with high probability.

The Lan-DeMets methodology is flexible in that the total number and timing of the interim looks does not need to be specified in advance. Based on results of periodic partial analyses additional looks can be planned and the test boundaries can be adjusted according to the spending function.

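### Table 4's efficacy boundaries are not O'Brien-Fleming: they match spending of 0.05·t², so the first look stops at Z = 2.57 where the named function requires 3.14

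*Supplement*

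**What the plan says.** Section G.3 of the protocol adopts the Lan-DeMets approach and names the function: "For the EAGeR trial the spending function corresponding to the O'Brien-Fleming procedure will be used". It explains the choice by saying of the boundaries that "they do not significantly change the overall power and are conservative early in the trial", and adds that an early crossing should need a very large difference between the arms.

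The calculations rest on "We assume throughout an alpha level of 0.05 and a sample size of 1600 women divided equally to the aspirin and placebo arms". Section G2.2 makes the primary test a two-sided Z test. On the results, G.3 says: "Table 4 gives the power for one or two interim looks and the Z-score boundaries, assuming PLB = 0.48 in the placebo arm", with a rate ratio of 1.20. The looks are at 0.45 and 0.60 of the period in which live births accumulate.

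Table 4 prints (boundaries; cumulative power):

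- one look at 0.45: ±2.571, ±2.010; 0.490, 0.964
- one look at 0.60: ±2.366, ±2.038; 0.718, 0.963
- two looks: ±2.571, ±2.485, ±2.050; 0.490, 0.696, 0.962

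The text then relies on the table, for example: "one interim look at 0.45 of events accumulation period will results in a very small loss of total power to 0.964". It goes on to propose the two-look design with total power 0.962.

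The separate interim-analysis chapter (section 1.1.2, Eq. 1.4) also gives an O'Brien-Fleming-type formula for the efficacy boundaries, citing the protocol. It prints no numerical efficacy boundaries.

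**The concern.** An O'Brien-Fleming-type boundary before the halfway point should be near or above 3. A value of 2.571 at t = 0.45 has a nominal two-sided p of 0.0101, which is far too lenient for that family.

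Table 4 is the only place in the documents with numerical efficacy boundaries. A monitoring board that saw Z = 2.8 at the first look would be past the threshold in the table and short of the threshold implied by the text. G.3 contemplates ending recruitment, ending follow-up, or moving the placebo arm to aspirin after a crossing, and none of these can be undone. The interim stopping probabilities and the final critical value in the table also belong to a different design from the one named.

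**Working it through.** **Inputs.** Two-sided alpha 0.05 and 800 women per arm (G.3, G2.2); p0 = 0.48 and RR = 1.20, so p1 = 0.576 (G.3); looks at t = 0.45, 0.60 and 1.00 (Table 4).

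**Method.** The first boundary solves 2·[1 − Φ(c1)] = α(t1). Each later boundary solves P0(no earlier crossing, |Z(tk)| ≥ ck) = α(tk) − α(tk−1), where Z(s) and Z(t) have correlation √(s/t) for s < t. This was done by recursive numerical integration.

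**Step 1: reproduce Table 4's boundaries.** The printed first-look values point to the function:

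- 2·[1 − Φ(2.571)] = 0.0101, and 0.05 × 0.45² = 0.010125, for which Z = 2.572
- 0.05 × 0.60² = 0.0180, for which Z = 2.366

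With α(t) = 0.05·t² throughout:

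| Looks | Table 4 | 0.05·t² |
|---|---|---|
| 0.45, 1 | 2.571 / 2.010 | 2.572 / 2.009 |
| 0.60, 1 | 2.366 / 2.038 | 2.366 / 2.039 |
| 0.45, 0.60, 1 | 2.571 / 2.485 / 2.050 | 2.572 / 2.485 / 2.047 |

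Spending of 0.05·t, 0.05·t^1.5, 0.05·t³ and Pocock type was also tried. At 0.45 these give 2.282, 2.430, 2.837 and 2.188, so none fits.

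**Step 2: reproduce Table 4's powers.** With pooled variance and a continuity correction, p̄ = 0.528 and the drift is

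θ = (0.096 − 1/800) × √1600 / [2 × √(0.528 × 0.472)] = 3.796.

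Power at the first look is then Φ(3.796 × √0.45 − 2.571) = Φ(−0.025) = 0.490, as printed. Table 4's own boundaries give 0.490/0.964, 0.717/0.963 and 0.490/0.695/0.962, all within 0.001 of the table. The documents do not state this drift; it is inferred from the fit. The same correction gives 0.774, 0.809 and 0.842 for the RR 1.15 column of Table 3, which prints .77, .81 and .84.

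**Step 3: the named function.** The standard two-sided form is α(t) = 4 − 4Φ(2.2414/√t), where 2.2414 is z at 1 − 0.05/4.

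- t = 0.45: 2.2414/√0.45 = 3.341, so α = 0.0017 and the boundary is 3.144
- t = 0.60: 2.2414/√0.60 = 2.894, so α = 0.0076 and the boundary for a single look is 2.669

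| Looks | Boundaries | Cumulative power, θ = 3.796 | Cumulative power, θ = 3.864 |
|---|---|---|---|
| 0.45, 1 | 3.144 / 1.965 | 0.275 / 0.967 | 0.291 / 0.971 |
| 0.60, 1 | 2.669 / 1.981 | 0.607 / 0.966 | 0.627 / 0.971 |
| 0.45, 0.60, 1 | 3.144 / 2.693 / 1.982 | 0.275 / 0.602 / 0.966 | 0.291 / 0.622 / 0.971 |

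The drift 3.864 is the one printed in section 1.2 of the interim-analysis chapter (unpooled variance, no correction).

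**Step 4: other readings of O'Brien-Fleming at t = 0.45.** The form 2 − 2Φ(1.96/√t) as a two-sided total gives 2.922. Classic O'Brien-Fleming boundaries give 2.94 (one look) to 2.98 (two looks). Eq. 1.4 taken literally gives 3.341. None comes near 2.571.

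**Step 5: size on the outcome scale.** Suppose t = 0.45 means 0.45 × 800 = 360 women per arm, with a pooled rate near 0.5. The standard error is √(2 × 0.25/360) = 0.0373. Then 2.571 corresponds to an observed difference of 9.6 percentage points, and 3.14 to 11.7. The first is simply the assumed design effect (0.576 − 0.48 = 0.096), which is why the stated chance of stopping is about one half.

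**The case against.** The strongest reply is that Table 4 is a planning illustration. Under Lan-DeMets the boundary at each look is calculated from the named function at the actual information fraction. The documents name only O'Brien-Fleming, in G.3 and again through the form of Eq. 1.4. On that view there is one rule and a table that fails to match it. In addition, Table 4's two-look boundaries spend 0.0497 in total, so type I error is controlled. Final power differs by only 0.004, and G.3 says the board will weigh more than the test.

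Much of this is true. Overall alpha is not inflated, the sample size is unaffected, and the conclusion that interim looks cost little power survives. Z = 2.57 would take effect only if someone used Table 4. The objection does not remove the fault, however. G.3 adopts the two-look design with the total power from that table, and no corrected boundaries appear anywhere else. Flexibility in timing changes the boundaries of a given function; it does not change the function. A board's discretion still needs one unambiguous reference value.

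Two technical reservations also stand. The attribution to 0.05·t² is inferred from the numbers, although the mismatch with O'Brien-Fleming does not depend on it. The replacement powers depend on the drift, as the last two columns in step 3 show; the boundaries do not.

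**Conclusion.** The concern holds. Table 4 contradicts the spending function and the rationale stated in the same section.

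- At t = 0.45 the printed boundary is 2.571, against 3.144. Error spent is 0.0101 against 0.0017, a ratio of about 6.
- The stated chance of stopping at 0.45 when RR = 1.2 is 0.490, against 0.275 (0.291 with the drift printed in the interim-analysis chapter).
- In the two-look plan, cumulative power by 0.60 is stated as 0.696, against 0.602 (0.622). The final critical value is 2.050, against 1.982.

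These figures assume the standard two-sided O'Brien-Fleming-type form with a total of 0.05, and looks at exactly 0.45 and 0.60. Eq. 1.4 as printed reaches only 2 − 2Φ(2.2414) = 0.025 at t = 1. It delivers the stated 0.05 only if read per side, and that reading gives 3.144.

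**What to change.** Replace Table 4 with the O'Brien-Fleming values, and state the variance formula and any continuity correction behind the powers. With the drift that reproduces the present table:

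- one look at 0.45: ±3.144 / ±1.965; power 0.275 / 0.967
- one look at 0.60: ±2.669 / ±1.981; power 0.607 / 0.966
- two looks: ±3.144 / ±2.693 / ±1.982; power 0.275 / 0.602 / 0.966

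Update the sentences that quote 0.964 and 0.962, and use the same values in the monitoring board's rule. Write Eq. 1.4 so that it reaches 0.05 at t = 1. State that boundaries will be recalculated from it at the actual look, and choose one time scale: G.3 uses elapsed time, while the interim-analysis chapter uses the fraction of participants completed.

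If 0.05·t² was in fact intended, the alternative is to name it and withdraw the claim of early conservatism.

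The cost is one table, a few sentences and one formula. No participants are added and final power rises slightly. The only loss is a lower stated chance of stopping early.
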